### Trial design {8}

This study is a phase IIb randomised, double-blind clinical trial type study. It will be a parallel design where two groups receive two treatments (interventions). We will study the characteristics of the factors and effects. In this manner, this analysis will allow us to conceptualise the design as a 2 × 3 mixed factorial. Thus, we will include a factor between groups (type of intervention, two levels) and an intra-subject factor (measured in three episodes, one pre-intervention, and two post-intervention). Based on the factor between groups, it will implement two different interventions. The treatment group will receive a cognitive training intervention combined with alternating current electrical stimulation (i.e. treatment). The control group will receive a traditional cognitive training intervention with placebo electrical stimulation. Depending on the intra-subject factor, two dependent variable measurements will be implemented: one pre-intervention and one post-intervention measure. This design will allow the study of the potential interaction effects between the inter- and intra-subject factors [35].

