### Sample size {14}

For the estimation of the minimum required sample size, we will consider the following parameters: (a) Effect size for the mixed ANOVA statistical test (2 × 2, with interaction effects), (b) Statistical power (1 − *β*) = 0.95 and (c) Significance level α = 0.05. We will use the G*Power 3 software to calculate [47]. Considering an effect size *η*^2^ = 0.06, the sample size amounts to 54 participants (n1 = 27; n2 = 27). As our study will be a two-intervention effect, we will consider an effect size somewhat smaller than those observed for comparisons between clinical populations of prefrontal theta oscillations during working memory: for example, Lenartowicz: *η*^2^ = 0.09 [38], and which coincides with the work of our team *η*^2^ ~ 0.1 [28]. The effect size we will use to calculate the sample is considered a moderate to significant effect according to Cohen’s criteria [48]. However, the initial sample size we propose in this project finds the proportion of participants who may present low adherence to the study. In this regard, we can point out that in a preliminary study with similar characteristics, a drop-out rate of about 15% was observed. Therefore, considering the drop-out percentage and the minimum sample size required to investigate an effect, the initial sample will be 62 participants (n1 = 31; n2 = 31).

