The effect sizes will be reported for each electrophysiological and cognitive performance measure analysis through the index η^2^p (partial eta square). The respective post hoc comparisons will use Bonferroni’s correction, and the effect size will be reported through Cohen’s index *d*. Graphs of the interaction effects will be provided if observed. In case of transgression of the sphericity assumption, the Greenhouse–Geisser correction will be made. Consequently, the respective parametric statistics will be provided (i.e. Friedman test, Connover’s post hoc tests). For all hypothesis tests, a significance level will be considered *⍺* = 0.05.

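### Holm's step-down correction would be a cheap, optional gain over single-step Bonferroni for the post hoc comparisons

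*Protocol article*

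**What the plan says.** The protocol article tests the group-by-time interaction first and then follows it up. For the follow-up, the Inferential analysis section states: "The respective post hoc comparisons will use Bonferroni’s correction". The same paragraph applies 0.05 throughout ("For all hypothesis tests, a significance level will be considered"). Time has three levels: Trial design {8} describes "an intra-subject factor (measured in three episodes, one pre-intervention, and two post-intervention". The Outcomes section places the two post-intervention visits at 1 and 12 weeks.

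The sample size does not rest on these comparisons. Sample size {14} takes the "Effect size for the mixed ANOVA statistical test (2 × 2, with interaction effects" as its basis, with "Statistical power (1 − *β*) = 0.95", "Significance level α = 0.05" and an assumed eta squared of 0.06, and concludes that "the sample size amounts to 54 participants". That is raised to 62 for drop-out. The article does not list which post hoc comparisons form the family. That detail is commonly left to an analysis plan and is not criticised here.

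**The concern.** With three visits, a significant interaction does not say when the arms differ. The post hoc comparisons have to show whether an effect is present at 1 week, at 12 weeks, or at both. An effect that appears early and persists makes at least two comparisons real at once. In that situation single-step Bonferroni gives up power, because it keeps testing every comparison at 0.05/m after one has already been rejected. Holm relaxes the threshold after each rejection, uses the same p-values and family, and needs no extra assumption. What is at stake is the power to show that an effect is both present and lasting, in a trial of about 26 to 27 completers per arm. Type I error control and the primary test are not at stake.

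**Working it through.** **1. The plan's own figure.** Inputs from Sample size {14}: eta squared 0.06, alpha 0.05, power 0.95, two groups and two measurements. The correlation between measurements is not given; 0.5 is assumed.

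- f² = 0.06/(1 − 0.06) = 0.0638.
- Noncentrality = f² × N × m/(1 − rho) = 0.0638 × 54 × 2/0.5 = 13.8, with 1 and 52 degrees of freedom.
- Power = 0.954, so N = 54 reproduces. At other correlations N would be 104 (rho 0), 74 (0.3) or 34 (0.7).
- Enrolling 62 with 15% drop-out leaves 62 × 0.85 = 52.7, about 26 per arm.

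No post hoc threshold enters this calculation, so changing the correction leaves 54 and 62 as they are.

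**2. The two rules.** For m comparisons, Bonferroni tests each at 0.05/m. Holm orders the p-values and tests the j-th smallest at 0.05/(m − j + 1), stopping at the first failure.

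- m = 2: Bonferroni 0.025, 0.025; Holm 0.025, 0.05.
- m = 3: Bonferroni 0.0167 three times; Holm 0.0167, 0.025, 0.05.

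The first step is the same, so the chance of at least one rejection is the same. Holm can only add rejections after that.

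**3. Size of the gain on a common scale.** Assumptions, none of them from the documents: normal test statistics, two-sided tests, each real comparison with 80% power at unadjusted 0.05 (mean 1.96 + 0.84 = 2.80), correlation 0.5. Bonferroni power per comparison follows directly:

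- m = 2: Φ(2.80 − 2.241) = 0.71.
- m = 3: Φ(2.80 − 2.394) = 0.66.

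Holm was simulated (one million draws per row):

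| Family | Each real comparison, Bonferroni → Holm | All real effects shown | At least one rejection |
|---|---|---|---|
| Two, both real | 0.71 → 0.76 | 0.57 → 0.68 | 0.853 both |
| Three, two real (group differences, baseline null) | 0.66 → 0.69 | 0.51 → 0.57 | 0.817 both |
| Three, two real (pairwise visits, persisting effect) | 0.66 → 0.69 | 0.51 → 0.57 | 0.810 both |
| Two, one real | 0.713 → 0.714 | same as per comparison | 0.723 both |
| Three, one real | 0.659 → 0.660 | same as per comparison | 0.672 both |

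For the pairwise-visit row the correlations are 0.5, 0.5 and −0.5, as differences between three equally correlated visits require.

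Check for the family of two: at least one = sum of the two powers − both. Bonferroni: 0.713 + 0.712 − 0.572 = 0.853. Holm: 0.765 + 0.765 − 0.677 = 0.853.

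**4. Size of the gain at this trial's sample size.** Simulated t tests, 27 per arm, within-person correlation 0.5 (assumed), family of three group differences with a null baseline difference and the same standardised difference d at both post-intervention visits (assumed range):

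| d | Each real comparison | Both shown | Error on the true null |
|---|---|---|---|
| 0.5 | 0.27 → 0.29 | 0.13 → 0.17 | 0.017 → 0.028 |
| 0.7 | 0.54 → 0.58 | 0.38 → 0.44 | 0.017 → 0.034 |
| 1.0 | 0.88 → 0.90 | 0.80 → 0.85 | 0.018 → 0.043 |

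With all three null, the family-wise error was 0.045 under both rules. Within-arm paired comparisons gained about 0 to 10 points each, and about 7 to 10 points for showing both changes from baseline.

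**The case against.** The strongest reply is that nothing here is wrong. Bonferroni is prespecified and valid, no stated figure depends on it, and the article plans no power for any post hoc comparison. All of that stands, and so does the fact that the chance of at least one rejection is identical.

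A reader might go further and infer that the plan contains an error, that the main analysis loses power, or that the trial is too small because of this choice. The documents do not support that: the sample size rests on the interaction test, which uses no correction.

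A reader might also expect a larger gain by supposing that three or more comparisons are all real, equally strong and equally correlated. The natural families of three do not fit that picture. A baseline group difference is null under randomisation. Among pairwise visit differences one is the sum of the other two, so with equal standard errors three equal non-zero standardised effects cannot occur.

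Two smaller points also stand. When some effects are real, Holm uses more of the error allowance than Bonferroni, though still within 0.05. And Bonferroni has simple simultaneous confidence intervals that agree with its p-values, so preferring it for that reason is legitimate. The article, however, promises Cohen's d for these comparisons and does not mention simultaneous intervals, so no stated deliverable would be lost.

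**Conclusion.** The point holds as an optional efficiency improvement to a valid plan. Holm dominates single-step Bonferroni on the same family and alpha, and the benefit falls on the question these comparisons serve: whether an effect is present at both 1 and 12 weeks. Under the 80% power assumption the gain is about 5 points per comparison and 10 to 11 for showing both in a family of two, and about 3 and 6 to 7 points in a family of three with two real effects. It is near zero if only one effect is real. The size depends on assumed effects, correlation and family size, since the article gives none of these for the post hoc comparisons. The direction does not depend on them: Holm never rejects less.

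**What to change.** In the Inferential analysis section, replace Bonferroni's correction by Holm's step-down correction for the post hoc comparisons, with the same family and alpha = 0.05. If confidence intervals are reported, either label them as unadjusted or give Bonferroni simultaneous intervals, and note that they may not agree with the Holm-adjusted p-values in every case.

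The cost is a change of name in the plan and one option in the software. There is no change to the sample size or to the primary test. The one downside is that simultaneous intervals that match Holm exactly are less simple than Bonferroni's.

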### Interim analyses {21b}

A committee focused on data monitoring and ethics will regularly review outcome data throughout the data collection process.

### Methods for additional analyses {20b}

We do not intend to conduct subgroup analyses.

### Methods in analysis to handle protocol non‐adherence and any statistical methods to handle missing data {20c}

The statistical analyses, including mixed models and Bayesian estimation, will be conducted without resorting to ad hoc imputations to manage missing data resulting from participant drop-out and to perform efficacy analysis. Little’s MCAR test will determine whether the missing data are completely at random, ensuring the robustness of the analyses even without data imputation.

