### Outcomes {12}

#### Primary outcome

The primary result will be prefrontal theta oscillatory activity. This continuous variable is sensitive to electrophysiological changes underlying cognitive processes as WM. It has been described in several works of our group and others [28, 38–43]. The primary timepoint for outcome measures will be three times: pre-intervention, 1 and 12 weeks post-intervention. This outcome corresponds to the ratio of the normalised power (mean/standard error, mV^2^) of the prefrontal theta oscillation (5–10 Hz, F3 electrode) related to successful memory performance (SMP). This prefrontal theta oscillation is calculated based on a single-trial general linear model that includes SMP as the regressor of interest and memory load as a secondary regressor.

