#### Inferential analysis

Compliance with assumptions for parametric testing will be contrasted. In particular, univariate normality (i.e. Kolmogorov-Smirnoff, Shapiro–Wilk), sphericity (i.e. Mauchly’s W), and homoscedasticity of error variances (i.e. Levene test). If any of the above assumptions are violated, the corresponding non-parametric estimates will be provided. Mixed-model analyses without any ad hoc imputations will be used to handle missing data in case of participant drop-out and to conduct the efficacy analysis [53]. To assess distributional assumptions and the impact of missing random effect components on the model, several tests will be conducted. Normality assumptions will be examined using the Shapiro–Wilk test, skewness and kurtosis indices, and normality plots (Q-Q plots). Homoscedasticity will be investigated using Levene’s test and Box’s M test for equivalence of covariance matrices. The Wald statistic (or *Z*-test) will be utilised to test residual error variance estimation and the null hypothesis of homogeneity of residuals. The assumption that data is missing completely at random (MCAR) will be assessed using Little’s MCAR test, which remains robust to violations of distributional assumptions [54]. Additionally, the primary outcome will be evaluated using Bayesian hierarchical approaches employing JAGS and R software. In this approach, each individual beta per regressor will be subjected to a population distribution of beta values that follow a normal distribution [55]. The prior assumption for each population distribution of beta values will be flat (non-informative). The correct convergence of the Markov Chain Monte Carlo (MCMC) will be evaluated using the Gelman-Rubin statistic. The model fit will also be assessed using DIC (Deviance Information Criterion) and LOOIC (Leave-One-Out Information Criterion).

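### The missing-data section relies on Little's MCAR test to ensure robustness to drop-out, a conclusion that neither result of the test can support

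*Protocol article*

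**What the plan says.** Two sections of the protocol article deal with drop-out.

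- **Inferential analysis:** "Mixed-model analyses without any ad hoc imputations will be used to handle missing data in case of participant drop-out and to conduct the efficacy analysis". The same paragraph names MCAR as the assumption to be checked: "The assumption that data is missing completely at random (MCAR) will be assessed using Little’s MCAR test, which remains robust to violations of distributional assumptions". It attaches no action to the result.
- **Section {20c}, non-adherence and missing data:** mixed models and Bayesian estimation are again planned without imputation. The section closes by saying that Little's "MCAR test will determine whether the missing data are completely at random, ensuring the robustness of the analyses even without data imputation".

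Neither section names MAR or mentions drop-out that depends on unobserved outcomes. On the expected amount of missing data, the sample size section reports that in a similar preliminary study "a drop-out rate of about 15% was observed", and it plans 62 participants, 31 per arm.

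**The concern.** The sentence in {20c} contains two errors of inference.

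1. A hypothesis test can give evidence against MCAR but cannot show that MCAR holds. Non-rejection with few drop-outs is weak evidence.
2. MCAR is not the condition on which the planned analysis rests. A correctly specified likelihood mixed model is valid under MAR, that is, when drop-out depends only on data that are observed and in the model. The threat is drop-out that depends on values never seen (MNAR). Little's test compares observed values between missingness patterns, so it cannot tell MAR from MNAR.

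What is at stake is what the trial may conclude about drop-out. Read as written, a non-significant test could be reported as showing robustness when the arm difference is biased. A significant test could be taken as a mark against a model that is valid.

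**Working it through.** **Inputs from the protocol.** 62 participants, 31 per arm; drop-out about 15%; on timing, "The primary timepoint for outcome measures will be three times: pre-intervention, 1 and 12 weeks post-intervention". Expected drop-outs: 62 × 0.15 = 9.3, so about 9, leaving 53. The disputed sentence itself gives no figure to reproduce.

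**Assumptions, not in the protocol.** Outcome SD of 1, correlation 0.5 between visits, and the drop-out mechanisms below. In the first set of simulations only baseline and week 1 are used, and the 9 drop-outs have baseline only.

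**What the test sees.** With two patterns (complete; baseline only), the degrees of freedom are (2 + 1) − 2 = 1. With maximum-likelihood estimates for monotone data, the statistic reduces to a comparison of baseline means:

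d² = (9 × 53 / 62) × (baseline mean of drop-outs − baseline mean of completers)² / s² = 7.69 × (difference in SD)²

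It rejects at 5% when d² exceeds 3.84, that is, when the observed baseline difference exceeds √(3.84 / 7.69) = 0.71 SD. No missing week-1 value enters it.

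**Power for a baseline difference.** For a true difference of 0.5 SD, the noncentrality is 0.5 × √7.69 = 1.39. A two-sided t test of 9 against 53 then has power of about 28%. Non-rejection is therefore the likely result even when MCAR is false by that amount.

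**Simulation, baseline and week 1, 4,000 runs per scenario.** Correlation here means that between the driver named and the tendency to drop out.

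| Drop-out depends on | Test rejects | Bias of mixed-model arm difference |
|---|---|---|
| Nothing (MCAR) | 5 to 6% | none |
| Observed baseline, correlation 0.3 to 0.5 (MAR) | about 34 to 75% | none |
| Unseen week-1 value in one arm, correlation 0.5 to 0.9, 5 of 9 drop-outs in that arm | about 11 to 22% | from about 0.11 SD |
| The same, all 9 in that arm | about 14 to 40% | up to about 0.33 SD |
| Only the part of week 1 that baseline does not predict, one arm, correlation 0.3 to 0.9 | about 5% | about 0.12 to 0.37 SD |

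**Simulation, three visits.** This used 15% drop-out, logistic drop-out with log-odds slopes of 1 to 2 per SD, and the arm difference in change from baseline to 12 weeks.

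- MAR on baseline: rejection 53 to 95%, no bias. MAR on the 1-week value: 62 to 97%, no bias.
- MNAR on the unpredicted part of the 12-week value, in opposite directions by arm: rejection 4.4 to 4.5%, bias 0.22 to 0.32 SD. With 2,000 participants and slope 2, rejection is still 5.3% and bias 0.33 SD, so this is not merely low power.
- MNAR on the 12-week value in the treated arm only (30% drop-out there): rejection 14 to 29%, bias 0.17 to 0.27 SD. At correlation 0.7 and slope 2, rejection reaches 48%.

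The empirical standard error of the estimate at correlation 0.5 and 15% drop-out is about 0.27 to 0.28 SD, so the larger biases are about one standard error. Across these scenarios, frequent rejection goes with an unbiased model at least as often as with a biased one.

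**The case against.** **No decision hangs on the test.** This stands. Both sections commit to the mixed model without imputation whatever the test shows. A reader might infer that the primary estimate or p-value depends on the MCAR result; the protocol does not say so. The exposure is the interpretation written into {20c}.

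**The test is not blind to all informative drop-out.** This also stands. A reader might infer that it never rejects above its 5% level when drop-out depends on unseen values. That is true only for the part of the outcome that earlier visits do not predict. If drop-out depends on the whole unseen value, baseline carries a trace and the test has partial power, as the table shows. Even then it usually misses the problem, and a rejection would look the same as one caused by harmless MAR drop-out.

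**Sensitivity analyses belong in the analysis plan.** A reader might infer that the trial has no MNAR analysis. That cannot be concluded, because the analysis plan is not shown and this is a condensed article. The point rests on the affirmative claim in {20c}, which an analysis plan that followed it would inherit.

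**MCAR does matter for the rank-based fallback** ("i.e. Friedman test, Connover’s post hoc tests"), which needs complete cases. It is more relevant there, but non-rejection cannot confirm it there either. In the three-visit simulation, drop-out on baseline in opposite directions by arm biased the complete-case arm difference in change by 0.13 to 0.21 SD in size, while the test rejected in only 9 to 16% of trials.

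**The core method is sound.** Agreed: a mixed model without ad hoc imputation is standard and valid under MAR, and the protocol supports retention with reminder calls and transport.

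**Conclusion.** The claim in {20c} is wrong as written. Little's test cannot determine that data are MCAR, MCAR is not what the mixed model needs, and neither result of the test shows that the analysis is robust. The planned model and the primary estimate are unaffected; the stated robustness check is what fails.

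The illustrated biases of about 0.11 to 0.37 SD (two-visit simulations) rest on assumed correlations, assumed drop-out mechanisms and an assumed split of drop-outs between arms. They show what the test can miss and do not estimate bias in this trial. From the protocol come only the 62 participants, the drop-out of about 15% and the visit schedule. The three points of logic do not depend on the simulations. The change should be made, because it alters what the trial may claim about drop-out.

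**What to change.** 1. Delete the clause in {20c} that makes the test the guarantee of robustness.
2. State that the mixed model, and likewise the Bayesian model, assumes MAR given the observed data included in it.
3. Keep Little's test, if wanted, as a description of the missing data with no conclusion attached. Align the sentence under Inferential analysis, which now names MCAR as the assumption.
4. Examine robustness of the primary contrast with a simple MNAR sensitivity analysis. One option is a delta-adjusted (tipping-point) analysis: shift the unobserved post-intervention values by a range of amounts fixed in advance and report the shift at which the conclusion changes.

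The arithmetic of item 4 is light. A shift of δ in one arm's missing values moves that arm's mean by the proportion missing times δ. A 1 SD shift moves the arm difference by 5/31 = 0.16 SD if five of 31 are missing in that arm, or 9/31 = 0.29 SD if all nine are. It does not alter the imputation-free primary analysis.

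Cost: two sentences and one short extra analysis, with no new data.

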### Plans to give access to the full protocol, participant‐level data and statistical code {31c}

The sharing of data will be facilitated through a controlled access model, which adheres to the guidelines set forth by the Ethical Committee and recommendations provided by the Biomedical Informatics Center Clinica Alemana—Universidad del Desarrollo in Chile (https://redcap.cibm.cl). To gain access to the data for future projects, scientists must submit a formal request to the CI, and any project utilising the data must have received approval from the Ethical Committee and regulatory bodies overseeing the release of anonymised data. We will strictly adhere to current recommendations regarding anonymisation and curation of trial data for sharing purposes [56].

